## GLOSSARY OF TERMS

## ABBREVIATIONS

[illegible]

## STUDY SYNOPSIS

|                             |                                                                                                                                                                                                                                                                                                                                                     |
|-----------------------------|-----------------------------------------------------------------------------------------------------------------------------------------------------------------------------------------------------------------------------------------------------------------------------------------------------------------------------------------------------|
| Title of Study:             | Can continuous or intermittent normal saline nebulisation via a vibrating mesh nebuliser or intermittent normal saline via a standard jet nebuliser improve the lung physiology and secretion viscosity in mechanically ventilated patients with a Heat Moisture Exchange (HME) filter in the circuit?                                              |
| Study Centre:               | Queen Elizabeth University Hospital                                                                                                                                                                                                                                                                                                                 |
| Duration of Study:          | 12 months                                                                                                                                                                                                                                                                                                                                           |
| Primary Objective:          | Comparison of the viscosity of respiratory sections produced using a vibrating mesh nebuliser or a traditional jet nebuliser.                                                                                                                                                                                                                       |
| Secondary Objectives:       | 
 
• Volume of secretions
 
• Work of breathing
 
• Airway resistance
 
• Number of additional nebulised doses of saline or other drugs administered during the study period
 
• Nurse opinion of ease of sampling
 
• Frequency of HME filter change
 
             |
| Primary Endpoint:           | Viscosity of respiratory sections (assessed by the Qualitative Sputum Assessment Tool).                                                                                                                                                                                                                                                             |
| Rationale:                  | Nebulisation improves secretion management and respiratory physiology by reducing viscosity of respiratory secretions.                                                                                                                                                                                                                              |
| Methodology:                | Prospective randomised pilot study.                                                                                                                                                                                                                                                                                                                 |
| Sample Size:                | 60 patients                                                                                                                                                                                                                                                                                                                                         |
| Screening:                  | Patients ventilated via an endotracheal tube or tracheostomy in the Intensive Care Units of the Queen Elizabeth University Hospital and identified at the daily meeting between physiotherapists and nursing staff as having a secretion load.                                                                                                      |
| Registration/Randomisation: | Computer generated randomisation                                                                                                                                                                                                                                                                                                                    |
| Main Inclusion Criteria:    | 
 
• Patient aged 18-80 years at time of recruitment to study
 
• Ventilated via an endotracheal tube or tracheostomy with an HME filter in the circuit
 
• Secretion load defined as patient requiring suctioning of secretions at least 2 times in the 6 hours prior to recruitment.
 
 |

|                                         |                                                                                                                                                                                                                                                                                                                                                                                            |
|-----------------------------------------|--------------------------------------------------------------------------------------------------------------------------------------------------------------------------------------------------------------------------------------------------------------------------------------------------------------------------------------------------------------------------------------------|
|                                         | 
 
• Sputum viscosity grade 1 to 3 pourability in the Qualitative Sputum Assessment tool. (See below)
 
• Not yet received saline nebulisation in the previous 6 hours prior to recruitment
 
• Likely to be ventilated via an endotracheal tube or tracheostomy for at least 3 days in the opinion of the treating clinician
 
 |
| Main Exclusion Criteria:                | 
 
• Pregnancy
 
• Pulmonary embolus
 
• Heart Failure (NYHA Grade III/IV)
 
• Clinical evidence of frank pulmonary oedema
 
• Cardiovascular instability (systolic BP <math>\leq 75</math> or heart rate <math>\geq 140</math>)
 
                                                                                |
| Duration of Treatment:                  | Up to 72 hours                                                                                                                                                                                                                                                                                                                                                                             |
| Product, Dose, Modes of Administration: | 
Continuous nebulisation of 0.9% normal saline using the Aerogen Solo Nebuliser (50mls/24h via a syringe feed set)
OR
 
Intermittent nebulisation of 0.9% normal saline using the Aerogen Solo Nebuliser (5mls, 6 hourly) OR
 
Intermittent standard nebulisation using the Intersurgical Cirrus 2 self sealing Jet Nebuliser (5 mls, 6 hourly)
                        |
| Statistical Analysis:                   | Comparison of the difference in the viscosity of respiratory sections compared using Kruskal Wallis test with SPSS, release 19.0 for Windows; SPSS , Chicago, IL                                                                                                                                                                                                             |

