### Exclusion Criteria:

Pregnancy  
 Pulmonary embolus  
 Heart Failure (NYHA Grade III/IV)  
 Clinical evidence of frank pulmonary oedema

Initial sample of sputum obtained and Qualitative Sputum Assessment undertaken as follows:

| Volume (mls) |                                                                                                   |                      |  |
|--------------|---------------------------------------------------------------------------------------------------|----------------------|--|
| Type         | M, Muroid (no evidence of pus)                                                                    |                      |  |
|              | P, Purulent (uniformly purulent)
(Colour also recorded)                                        | Predominantly yellow |  |
|              |                                                                                                   | Predominantly green  |  |
|              | MP, Mucopurulent (mixed)
(Divided into 3 grades depending whether pus or mucus is predominant) | MMP                  |  |
|              |                                                                                                   | MP                   |  |
|              |                                                                                                   | MPP                  |  |
| Pourability  | Grade 1 - adheres closely to the container                                                        |                      |  |
|              | Grade ½(1.5)                                                                                      |                      |  |
|              | Grade 2 - moves slowly with gravity                                                               |                      |  |
|              | Grade 2/3(2.5)                                                                                    |                      |  |
|              | Grade 3 – slides in one mass                                                                      |                      |  |
|              | Grade ¾(3.5)                                                                                      |                      |  |
|              | Grade 4 – pours easily but may have viscid particles                                              |                      |  |

Randomisation

10

[figure not shown]

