### **3.2 Inclusion criteria**

- Patient aged 18-80 years at time of recruitment to study
- Ventilated via an endotracheal tube or tracheostomy with an HME filter in the circuit

- Secretion load defined as patient requiring suctioning at least 2 times in the 6 hours prior to recruitment
- Sputum viscosity with grades 1 to 3 pourability in the Qualitative Sputum Assessment tool
- Not yet received saline nebulisation in the 6 hours prior to recruitment
- Likely to be ventilated via an endotracheal tube or tracheostomy for at least 3 days in the opinion of the treating clinician

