### **4.2 Study Outcome Measures**

#### **4.2.1 Primary Outcome Measure**

- Median change of all viscosity (pourability) of respiratory secretions as assessed by a dedicated team or physiotherapists using the Qualitative Sputum Assessment Tool Scores taken at 10:00 and 16:00 while the patient is recruited to the study

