## **7.6 Sample size**

This is a pilot feasibility study and a total of 20 patients in each group is adequate to provide information to power a definitive study. The chosen samples sizes can be further justified as follows:

We will determine if the primary end point (viscosity even you are looking at the change in the score from baseline to final measurement, assuming the score is 1 to 4 in 0.5 increments at each time point, the distribution in values of change could range from -3 to +3 in 0.5 increments. This can therefore be treated as a continuous measurement. With 20 subjects we estimate an 80% power to detect a difference between any 2 groups of 0.503 per standard deviation (effect size=0.503) for the change in score. This assumes a significance level (p value) of 0.0167 to take into account that we would use 3 comparisons:

1. (Intermittent standard nebulisation vs. Continuous Aerogen nebulisation,
2. Intermittent standard nebulisation vs. Intermittent Aerogen nebulisation,
3. Continuous Aerogen nebulisation vs. Intermittent Aerogen nebulisation)

The statistically analysis and powering of this study were based on advice for [name] senior statistician the Robertson Centre, 24th July 2019.

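### The only primary test the protocol names is valid but leaves out the pre-randomisation pourability grade, which costs precision and leaves 20-per-arm comparisons exposed to chance baseline imbalance

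*Protocol*

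**What the plan says.** The Statistical Analysis row of the synopsis names one test: "Comparison of the difference in the viscosity of respiratory sections compared using Kruskal Wallis test". Section 7.2 gives a target of 0.5 on the pourability scale but no test.

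The quantity tested is a change score. Section 4.2.1 defines the outcome as "Median change of all viscosity (pourability) of respiratory secretions", using the 10:00 and 16:00 assessments. Section 7.6 works with the "change in the score from baseline to final measurement".

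A baseline grade exists for every patient. The flow chart places this step before randomisation: "Initial sample of sputum obtained and Qualitative Sputum Assessment undertaken as follows". Section 3.2 makes the grade an entry condition: "Sputum viscosity with grades 1 to 3 pourability in the Qualitative Sputum Assessment tool".

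On the scale, section 7.6 proceeds "assuming the score is 1 to 4 in 0.5 increments at each time point" and concludes that "the distribution in values of change could range from -3 to +3 in 0.5 increments". It also says that "a total of 20 patients in each group is adequate to provide information to power a definitive study". Section 7.1 says the pilot is not powered for formal comparison of the groups, and section 7.7 refers to a statistical analysis plan, which is not shown here.

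**The concern.** Kruskal-Wallis on change uses the baseline grade only by subtracting it. On a scale bounded at 1 and 4, the room to change depends on where a patient starts. Someone entering at grade 3 can rise by at most 1. Someone entering at grade 1 can rise by up to 3 and cannot fall. Change is therefore negatively related to baseline even when no treatment works.

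In arms of 20, with no stratification by entry grade described in section 9.1, the arms may differ in entry grade by chance, and the subtraction carries part of that difference into the contrast. Two things are at stake: the precision of the between-arm estimates that a definitive study would build on, and how an observed difference should be read if entry grades turn out unbalanced.

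**Working it through.** **Inputs from the protocol.** Scale 1 to 4 in steps of 0.5 (7.6); entry grades 1 to 3 (3.2); 20 per arm, three arms (7.6); shift of interest 0.5 grade (7.2); alpha 0.0167 for each of three pairwise comparisons (7.6). The correlation rho between baseline and post-baseline grade, and the spread of the grades, are not given. They are assumptions below.

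**The protocol's own figures.**
- *Range of change.* The stated lower limit comes from 1 - 4 = -3, which needs an entry grade of 4. With entry at 1 to 3 the limits are 1 - 3 = -2 and 4 - 1 = +3. This takes baseline to be the eligibility sample.
- *Power.* The stated 80% at 0.503 SD does not reproduce. For 20 per group and two-sided alpha 0.0167, power is 21% (normal approximation) or 19% (t), and 80% needs a difference of about 1.06 SD (t). That is a separate matter. It is noted so that 80% is not taken as the starting point for the gains below.

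**Analytic gain.** With equal SD (sigma) at baseline and follow-up, the variance per patient is 2 sigma^2 (1 - rho) for change and sigma^2 (1 - rho^2) after adjustment. The ratio is (1 - rho^2) / [2(1 - rho)] = (1 + rho)/2, which is 0.65, 0.75 and 0.85 at rho 0.3, 0.5 and 0.7. The entry cap makes the baseline SD smaller than the follow-up SD, so these ratios overstate the gain here.

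**Gain on the bounded scale.** Two arms of 20 were simulated with latent mean 2.2 and SD 0.9 (both assumed), grades rounded to 0.5 and limited to 1 to 4, entry at grade 3 or below, one post-baseline score per patient, a 0.5-grade shift and alpha 0.0167. The rank test on change was compared with ANCOVA on baseline grade.

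| rho (assumed) | Variance ratio, adjusted to change | Effective n per arm (20 / ratio) | Power, rank test on change | Power, ANCOVA |
|---|---|---|---|---|
| 0.3 | 0.75 | 20/0.75 = 27 | 16% | 24% |
| 0.5 | 0.83 | 20/0.83 = 24 | 23% | 29% |
| 0.7 | 0.92 | 20/0.92 = 22 | 36% | 41% |

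The ratio is near 1 by rho 0.9. With no treatment effect, baseline and change correlate at about -0.51, -0.43 and -0.33 for the three values of rho.

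**Three-arm check of the named test.** With latent mean 2 and SD 0.8 (assumed), a 0.5-grade shift in one arm and alpha 0.05, power for Kruskal-Wallis on change against ANCOVA is 34 v 50% at rho 0.2, 47 v 58% at 0.5, 82 v 86% at 0.8 and 97 v 98% at 0.9. With no effect, type I error is 4.4 to 4.8% for Kruskal-Wallis and 4.8 to 5.0% for ANCOVA.

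**Chance imbalance.** The standard error of a baseline mean difference between two arms of 20 is sqrt(2/20) = 0.316 SD. Given an imbalance d, the follow-up difference is expected to move by rho x d, so the change contrast moves by (1 - rho) x d in the opposite direction. For d equal to one standard error, that is 0.7 x 0.316 = 0.22 SD, 0.5 x 0.316 = 0.16 SD and 0.3 x 0.316 = 0.09 SD at rho 0.3, 0.5 and 0.7 (equal SDs assumed).

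**The case against.** The strongest reply is that nothing here is an error. A rank test on change is valid under randomisation and is a defensible choice for a seven-level ordinal score. A reader might infer that the planned test is biased or unfair. The documents do not support that: type I error holds, and the unadjusted contrast is unbiased on average. It is off only conditionally, when the arms happen to differ at entry.

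Covariate adjustment is also often left to the statistical analysis plan, and the unseen plan may already contain it. That is a fair limit. But the synopsis does not leave the test open. It names one that cannot take a covariate, so if the plan adjusts, the synopsis needs aligning with it.

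The pilot status (7.1) weakens any argument from power, and the comparison stays well short of 80% at rho 0.3 to 0.7 with or without adjustment. It does not weaken the argument from precision, since the study is meant to inform a definitive trial.

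Three further points stand:
- A small part of the power gain, about 1 to 3 percentage points, comes from leaving ranks rather than from the baseline grade.
- Adjustment is not free of cost.
- A repeated-measures model of all post-baseline grades would replace the outcome in section 4.2.1 and add assumptions about correlation and early departure. The concern does not require that.

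Finally, the wrong range in 7.6 might be taken to undermine the sample size. It does not: the effect size there is in SD units, so correcting the range changes no result.

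**Conclusion.** The point holds as a worthwhile improvement, not as a flaw that invalidates the analysis. The protocol fixes an unadjusted test on change although the baseline grade is already required for entry.

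The direction of the gain is consistent across low and moderate correlations. Its size is uncertain: a variance reduction of about 25%, 17% and 8% at assumed rho 0.3, 0.5 and 0.7, and almost nothing by 0.9. These figures rest on an assumed latent distribution and on a single post-baseline score per patient, neither of which the protocol supplies.

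The range of change in 7.6 is inconsistent with the entry criteria. This is a minor correction.

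**What to change.** Keep the outcome in section 4.2.1, read as each patient's median change over the scheduled scores, and state in the synopsis and section 7.2 that arms are compared with the pre-randomisation grade as a covariate. ANCOVA is the simplest form; rank-ANCOVA or an ordinal model is suitable if the bounded scale is a worry. Because baseline is constant within a patient, the median change equals the median post-baseline score minus baseline. ANCOVA on either therefore gives the same adjusted arm difference, and the endpoint need not be rewritten. Report the three adjusted pairwise differences with 95% confidence intervals, and keep Kruskal-Wallis on change as a sensitivity analysis.

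In section 7.6, change the range to -2 to +3.

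The cost is one degree of freedom, an assumption about model form (which the retained rank test helps to check) and a protocol amendment under section 12. No extra patients, visits or measurements are needed.

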## STUDY FLOW CHART

Patient screened in the Intensive Care Unit of the Queen Elizabeth University Hospital

### Inclusion Criteria:

Patient aged 18-80 years at time of recruitment to study  
 Ventilated via an endotracheal tube or tracheostomy with an HME filter in the circuit  
 Secretion load defined as patient requiring suctioning to remove respiratory secretions at least 2 times in the 6 hours prior to recruitment  
 Sputum viscosity with grades 1 to 3 pourability in the Qualitative Sputum Assessment tool  
 Not yet received saline nebulisation in the 6 hours prior to recruitment  
 Likely to be ventilated via an endotracheal tube or tracheostomy for at least 3 days in the opinion of the treating clinician

### Exclusion Criteria:

Pregnancy  
 Pulmonary embolus  
 Heart Failure (NYHA Grade III/IV)  
 Clinical evidence of frank pulmonary oedema

Initial sample of sputum obtained and Qualitative Sputum Assessment undertaken as follows:

| Volume (mls) |                                                                                                   |                      |  |
|--------------|---------------------------------------------------------------------------------------------------|----------------------|--|
| Type         | M, Muroid (no evidence of pus)                                                                    |                      |  |
|              | P, Purulent (uniformly purulent)
(Colour also recorded)                                        | Predominantly yellow |  |
|              |                                                                                                   | Predominantly green  |  |
|              | MP, Mucopurulent (mixed)
(Divided into 3 grades depending whether pus or mucus is predominant) | MMP                  |  |
|              |                                                                                                   | MP                   |  |
|              |                                                                                                   | MPP                  |  |
| Pourability  | Grade 1 - adheres closely to the container                                                        |                      |  |
|              | Grade ½(1.5)                                                                                      |                      |  |
|              | Grade 2 - moves slowly with gravity                                                               |                      |  |
|              | Grade 2/3(2.5)                                                                                    |                      |  |
|              | Grade 3 – slides in one mass                                                                      |                      |  |
|              | Grade ¾(3.5)                                                                                      |                      |  |
|              | Grade 4 – pours easily but may have viscid particles                                              |                      |  |

Randomisation

10

[figure not shown]

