### **3.3 Exclusion criteria**

- Pregnancy
- Pulmonary embolus
- Heart Failure (NYHA Grade III/IV)
- Clinical evidence of frank pulmonary oedema
- Cardiovascular instability (systolic BP  $\leq 75$  or heart rate  $\geq 140$ )

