## **4 Trial procedures**

### **4.1 Study schedule – Please see study flow chart**

#### **Visit 1: Screening**

- Assess if patient meets the entry criteria
- Give verbal and written information either to patient if they have capacity or legal representative.

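### The study flow chart lists four exclusion criteria where section 3.3 and the synopsis list five: cardiovascular instability is missing from the chart

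*Protocol*

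**What the plan says.** Exclusion criteria appear in three places in the protocol.

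- **Synopsis, main exclusion criteria.** Five entries: pregnancy, pulmonary embolus, NYHA grade III or IV heart failure, frank pulmonary oedema, and cardiovascular instability, the last defined by a systolic pressure at or below 75 or a heart rate at or above 140.
- **Section 3.3.** The same five entries, with the fifth opening "Cardiovascular instability (systolic BP" and giving the same two limits.
- **Study flow chart.** Four entries under an unqualified exclusion heading. The last is "Clinical evidence of frank pulmonary oedema", and the next line is already the following step: "Initial sample of sputum obtained and Qualitative Sputum Assessment undertaken as follows". Randomisation comes after that.

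Two further places bear on how the chart might be used. The heading of section 4.1, on the study schedule, says "Please see study flow chart". Under it, the Visit 1 instruction is "Assess if patient meets the entry criteria", without saying where those criteria are to be read. The schedule of assessments likewise calls for an eligibility review at Visit 1 and names no list.

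**The concern.** Eligibility should read the same wherever a protocol states it. Here a patient who meets only the fifth exclusion passes the list in the flow chart and fails the list in section 3.3, and no sentence in the protocol says which list takes precedence.

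The chart is more than a sketch. It begins with screening in the intensive care unit, sets out inclusion and then exclusion criteria, and leads through the baseline sputum assessment to randomisation. A busy member of staff could reasonably take it as a complete eligibility check. The omitted entry is also a substantive one: the protocol gave it numeric limits, and the trial recruits ventilated intensive care patients, in whom haemodynamic state is a realistic screening question.

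At stake are patient safety and clean eligibility: the possible randomisation, in breach of section 3.3, of a patient whom the protocol meant to keep out.

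**Working it through.** No formula applies. The check is a line-by-line comparison of the lists.

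| Exclusion | Synopsis | Section 3.3 | Flow chart |
|---|---|---|---|
| Pregnancy | yes | yes | yes |
| Pulmonary embolus | yes | yes | yes |
| Heart failure, NYHA III/IV | yes | yes | yes |
| Frank pulmonary oedema | yes | yes | yes |
| Cardiovascular instability | yes | yes | **no** |
| Count | 5 | 5 | 4 |

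The first four entries agree in all three places. The difference is 5 − 4 = 1 criterion.

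*Is the chart's list meant to be a shortened one?* Nothing says so. Its heading carries no qualifier. The synopsis does describe its own list as the main criteria, yet it includes the fifth entry. The chart's inclusion list is also complete: it has six entries, matching the six in section 3.2. A full inclusion list beside an exclusion list one line short looks like an omission and not a deliberate summary.

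*Could a line have been lost when the text was extracted?* This is possible but not indicated. The marker for a missing figure comes after the randomisation step and the page number. The exclusion list itself is plain text that runs directly into the sputum step.

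*What follows for a single patient?* Take someone who meets every inclusion criterion and only the cardiovascular exclusion. By section 3.3 or the synopsis that patient is ineligible. By the chart alone the same patient goes on to sputum sampling and randomisation.

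*Does any statistical quantity change?* No. The sample size reasoning in section 7.6 rests on group size, effect size, significance level and the number of comparisons. None of these depends on the exclusion list.

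*How many patients might be affected?* The protocol gives no prevalence of instability among screened patients, no screening volume and no rate at which staff would rely on the chart alone. Without these there is nothing from which to compute a number or a defensible range.

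**The case against.** The strongest reply is that this is an editorial slip in a summary chart. Two of the three places carry the criterion, including the section devoted to exclusion criteria, and the schedule of assessments separately requires an eligibility review at Visit 1. Section 5 adds continuous heart-rate and regular blood-pressure monitoring and lets the treating clinician stop nebulisation on any concern. Section 3.5 provides for withdrawal on similar grounds. Nothing in the endpoint or the analysis is touched.

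Much of this stands. It lowers the chance that an ineligible patient is enrolled and limits the exposure if one is. It does not remove the contradiction: monitoring after randomisation does not replace an entry criterion, and the Visit 1 review points to no particular list.

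Three stronger readings are tempting, and the protocol does not support them.

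- *That the chart is the list staff screen from.* Section 4.1 cites the chart for the study schedule. No passage tells staff to determine eligibility from the chart alone, so the consequence holds only for someone who does.
- *That the CRF shares the omission.* Section 9.2 says that a CRF was developed by the chief investigator, but its eligibility page is not shown. It may carry all five criteria, in which case much of the practical gap is already closed.
- *That a given number of ineligible patients would enter, die or stop early, and so add missing primary data.* The protocol provides no figure for the first part and makes no statement to support the second.

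**Conclusion.** The point holds as an internal contradiction in an operative eligibility rule. The flow chart gives four exclusions and the other two places give five; the absent one is cardiovascular instability. Anyone who screens from the chart alone could randomise a patient whom section 3.3 excludes.

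Its size is one criterion of five. The number of patients affected cannot be determined from the protocol, and sample size, power and error rate do not change. The conclusion rests on one assumption: that the extracted text of the chart is complete at the exclusion list, which its layout suggests. It does not depend on how the CRF is worded or on any view about which clinical limits are appropriate.

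This should be corrected because it concerns who may be randomised and costs very little to put right. It is not a flaw that threatens the trial's validity.

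**What to change.** Reconcile the synopsis, the study flow chart and section 3.3 so that all three carry one identical set of exclusions. Which clinical criteria belong in that set is for the investigator and sponsor to decide. Name the governing list in the Visit 1 text, so that the eligibility check has a single source.

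Confirm that the CRF eligibility page matches the reconciled list, and change it only if it does not. If any patient has already been screened from the flow chart, check that patient against the reconciled list and document the result.

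The cost is about one line of text in the list that changes and a short cross-reference at Visit 1, made through the amendment process in section 12, where the chief investigator and sponsor decide whether the change is substantial. No analysis or sample size work is needed.
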